**Discussion:**

The results of this randomised controlled trial with clinical assessments and multimodal MRI will help reveal the influence of Tuina treatment on the potential morphological changes in cortical and subcortical brain structures, the white matter integrity, and the functional activities and connectivity of brain regions of patients with KOA, which may provide scientific evidence for the clinical application of Tuina in the management of KOA.

**Trial registration:**

Chinese Clinical Trial Registry ChiCTR2000037966. Registered on Sep. 8, 2020.

**Dissemination:**

The results will be published in peer-reviewed journals and disseminated through the study’s website, and conferences.

## Background

Knee osteoarthritis (KOA) is an important cause of knee pain and disability, causing serious personal and social burden all over the world [1, 2]. The total prevalence of KOA is about 17.0% from 2007 to 2015 in China [3, 4]. With the aging of the population, the prevalence of symptomatic KOA is increasing [1, 2, 5, 6]. The elderly population is estimated to reach 480 million by 2050, and the negative impact caused by KOA pain is bound to increase in severity [4]. A previous study has pointed out a 660 million increase in years of life lived with disability (YLDs) from 1990 to 2010, during which period the prevalence of KOA increased [7]. Many patients with KOA experience chronic pain [8, 9]. Pain is a common occurrence throughout the development and symptomatic phase of KOA, thereby seriously limiting the quality of life of patients. Symptomatic KOA is associated with increased risk of all-cause mortality amongst the residents in the rural areas [1, 10]. Pain, as a typical manifestation and the most common complaint of patients with KOA, has become a hot topic in clinical and scientific research [1].

The International Society for the Study of Pain redefines pain as an unpleasant sensory and emotional experience associated with, or resembling that associated with, actual or potential tissue damage [11]. KOA pain is also multidimensional; it is produced by the peripheral and central nervous system, and the regulatory mechanism is complex [12, 13]. The manifestations of KOA chronic pain are complex and varied, such as persistent pain or intermittent pain, with or without neuropathological components, with or without central sensitisation [14]. A previous study has suggested that pain may be associated with the changes in the functional activity and structures of the cortical and subcortical brain regions in the acute and chronic pain [15].

Chronic pain of KOA is complex [16]. The brain plays a key role in the occurrence and relief of chronic pain as studies have shown brain plasticity changes (e.g., grey matter (GM) structure, white matter (WM) structure, and brain functional activities) after chronic pain by using multimodal magnetic resonance imaging (MRI) [17]. Central sensitisation, as an important manifestation and pathological change of the central nervous system, plays an important role in the pathogenesis of knee arthritis [18, 19]. With the extensive application of brain MRI technology in pain research, investigators have attempted to map the brain regions involved in the central pathogenesis of chronic pain, and partly explored the central mechanism of Tuina analgaesia [20, 21]. The chronic and persistent pain as the defining symptom of KOA is closely related to pathological changes in cortical structure and subcortical brain nuclei [22]. Diffusion tensor imaging (DTI) provides the microstructure changes in brain WM by measuring the displacement of water molecules across brain tissue components. Fractional anisotropy (FA) obtained from DTI describes the degree of anisotropy of a diffusion process, which can show the treatment effects associated with changes in the specific area of WM fibre using voxelwise statistics on skeletonised WM tracts [23].

Tuina is recorded in the classic work of ancient Chinese medicine *Huangdi Neijing*, which plays an important role in the health of Chinese people for thousands of years. It takes advantage of the hands of the therapist to manipulate the surface of the patient’s body. The relaxation techniques in Tuina such as pressing and kneading exert significant analgaesic effect, improving mood, improving patients’ confidence in prevention and treatment, promoting rehabilitation, and reducing the use of health services [24, 25]. Tuina can also relieve the pathological fatigue of muscles, restore the physiological balance of muscles and bones [26], regulate the expression of TNF-α, MMP-13, integrin α1, and integrin β1 to inhibit the apoptosis of chondrocytes, promote the metabolism of cartilage extracellular matrix, and inhibit the degeneration of articular cartilage [27]. Moreover, numerous domestic and foreign studies have also shown that education is conducive to the treatment of KOA [28–34].

An education programme such as a self-management programme can provide knowledge and skills that will come in handy in helping patients improve the management of their condition. Self-management skills are essential for treatment and are strongly recommended in the guideline for osteoarthritis management [35]. For most KOA patients, the daily care and health management falls onto the patient himself and the family, who are not expected to have a regular interaction with the professional healthcare system [36]. Previous studies have confirmed the effectiveness of education programmes in reducing pain and disability [37, 38]. By comparing the MRI outcomes to those who undergo Tuina intervention, the unique brain area where Tuina intervention is activated can be determined. The findings will help to explain the difference between Tuina intervention and health education intervention from the cerebral mechanism and provide ideas to maximise the benefits of Tuina therapy.

Tuina is a promising treatment option for KOA [1]. It is based on the theory of meridians and acupoints and modern anatomy. Many studies have shown that Tuina is safe and effective for KOA in terms of pain, stiffness, physical function, quality of life, articular cartilage wear, ligament damage, and inflammatory response [39–42]. As regards the well-documented effects on pain, Tuina is recommended for the prevention and cure of KOA by the Chinese guideline and expert consensus [1, 43]. Under the guidance of the theory of TCM, doctors primarily use their hands to do the standard Tuina Manipulation on the patient’s body surface, which can dredge channels and collaterals, activate qi and blood circulation, etc. to relief pain and other symptoms [44]. Tuina treatment could affect brain plasticity such as structure and functional activity in the patients with chronic pain [20, 21, 45–47].

However, studies on the longitudinal effect and central analgaesic mechanism of Tuina in patients with KOA chronic pain are few [20, 48–50]. The current study aimed to (1) investigate the brain alternations in KOA chronic pain patients with combined clinical assessments and structural, DTI, and fMRI techniques; and (2) explore the longitudinal mechanism of brain plasticity changes after Tuina pain relief treatment for KOA patients compared with healthcare education treatment.

## Methods/design

### Participant recruitment

All patients with KOA will be recruited from the Tuina department of Yueyang Hospital of Integrated Traditional Chinese and Western medicine, Shanghai University of TCM. Recruitment methods will include posters, online advertisements, and leaflets. Written informed consents will be collected taken from all patients. A total of 60 patients with KOA chronic pain will be randomly assigned into a Tuina group and an Education group at 1:1 ratio.

This study’s protocol has been approved by the Ethics Committee of Yueyang Hospital of Integrated Traditional Chinese and Western Medicine, Shanghai University of TCM. The trial was also registered to the Chinese Clinical Trial Registry.

### Study design

This is a single-centre and parallel randomised controlled trial. A total of 60 participants diagnosed with KOA based on the American College of Rheumatology (ACR) criteria (2019 revised version) [51] will be recruited as eligible patients. They will be randomly allocated into 2 equal groups with 30 patients per group, including a Tuina group and an Education group. The interventions of both groups will last for 30 min and be performed twice each week. The treatment period will be 12 weeks, and the follow-up period will be 48 weeks.

Outcome measurements and MRI scans will be assessed at the baseline and at 6 and 12 weeks after treatment, followed by 48 weeks of clinical follow-up. The changes in clinical variables and cerebral activity of each group will be analysed after data collection.

Evaluators and statisticians will be blinded to the group allocation during the procedure of outcome evaluation and data analysis [52, 53]. The trial flowchart and study design are shown in Figs. 1 and 2, respectively.

**Fig. 1 Fig1:**
[figure not shown]
Flow chart of the trial. The present study is a randomized controlled trial using multimodal MRI. Sixty KOA patients will be included and randomized equally to two groups, a Tuina group and an Education group. For 30 patients in each group, this trial will include a 12-week treatment period. During the treatment, patients in the Tuina group will receive 24 sessions of Tuina treatments, while the Education group will receive health care education. Both the outcome assessments and MRI scan will be performed at 3 time points, namely the baseline, the end of the treatments at 6 weeks and 12 weeks. Only the clinical outcomes will be assessed during 48 weeks of follow-up subsequently. The central mechanism of Tuina in the treatment of KOA will be analyzed after data collection

**Fig. 2 Fig2:**
[figure not shown]
Study schedule for data collection. The informed consent and examination will be conducted after recruitment. Then, matched KOA patients will be randomized into two groups and receive treatment. Both clinical outcomes and MRI scans will be performed at 3 time points. Only clinical data will be collected at 48 weeks of follow-up subsequently. Adverse events will be recorded in the case report form at any time during the study. *VAS* visual analog scale, *SF-MPQ* the Short-Form McGill Pain Questionnaire, *HAMD* Hamilton Depression Scale, *HAMA* Hamilton anxiety scale, *WOMAC* the Western Ontario and McMaster Universities Osteoarthritis Index, *SF-36* the Short Form 36 Health Survey scale

### Inclusion criteria

Meet the diagnostic criteria for KOA set by the ACR in 2019 [51]Are aged between 40 and 60 years, male or female, right-handed, with left knee painHave I–II degree knee joint radiological change on the Kellgren–Lawrence scaleHave an average knee pain score on a visual analogue scale (VAS) ≥ 3 (range from 0 to 10) in the past 3 monthsVolunteer to take part in the study and sign the informed consent formCan understand and follow the protocol.

Mainly to ensure the feasibility of the clinical study and the better baseline balance of the two groups, and because the incidence rate of KOA patients aged 40–60 is relatively high [54], so it is easier to recruit patients in the population aged 40–60. Since there are fewer patients with knee osteoarthritis under 40 years old, if patients under the age of 40 are recruited, the baseline of the two groups may not be easy to reach balance, and the age factor will also increase the difficulty of exploring the brain mechanism of knee pain. The patients older than 60 years old are more likely to develop pathological manifestations such as brain diseases and pain in other parts of the body [55], which also makes it more difficult to study and explore the brain mechanism of knee pain. According to our clinical observation, we found that there are more right-handed patients in the outpatient department of our hospital. Recruiting right-handed patients can avoid the influence of left-handed factors on the study results. Moreover, when patients with knee osteoarthritis have left knee pain, the brain signals detected are generally reflected in the patient’s right brain centre. If patients with right knee pain are recruited simultaneously, brain signals will also be detected in the left brain centre. However, this situation is not conducive to the combined calculation and statistical analysis of brain image data, nor is it conducive to revealing the precise range of brain areas of knee pain. Therefore, we will only recruit KOA patients who are aged between 40 and 60 years, male or female, right-handed, with left knee pain.

### Exclusion criteria

Are taking analgaesics or anaesthetics in the past 1 month that may influence brain-imaging outcomesHave received any other treatment in the past 1 month, such as exercising therapy, pharmacological intervention, or operationAre pregnant or lactating womenAre suffering from mental disease, neurological disease, infectious disease, gastrointestinal disease, cardiovascular and cerebrovascular disease, immunologic disease, respiratory disease or kidney disease, any other chronic pain symptoms, or have a history of brain injury with loss of consciousnessAre diagnosed as cancer, tuberculosis, rheumatism or rheumatoid arthritis, gout, or joint traumaHave MRI contraindications such as claustrophobia, cardiac pacemaker, defibrillator, heart stent, or intrauterine deviceHave skin lesion around the knee joint

### Suspension criteria

Are unsuitable to continue to participate in the study owing to adverse events or serious adverse events during the trialAre unsuitable to continue to participate in the study because of serious deterioration of disease or some complications and special physiological changesUses concomitant medication during the 12-week treatment period is a suspension criteria. Non-compliance to concomitant interventions will be monitored by daily dairies and WeChat queries.

### Dropout criteria

Withdrew from the studyLoss of contact

### Sample size

Sample size is required to compare two group mean values. The calculation method of bilateral equality of two samples is adopted [56] for two groups of A = Tuina group and B = Education group. Suppose H0: μA−μB=0, H1: μA−μB≠0. According to previous relevant research and pre-experiment results [39, 57], we expect the VAS significant score difference between and after 12 weeks of Tuina as μA = 3, and the VAS score difference between and after healthcare education intervention as μB = 0.7, assuming that the standard deviation *σ* of the two groups is equal, i.e., *σ*=2.1. If we set *α*=0.05 as the type I error, *β*=0.10 as the type II error, and 1−*β*=0.90 as the power, the final result is that we need at least 25 samples in each group. For the primary outcome, VAS will be assessed at baseline and at the end of 6 and 12 weeks of treatment, followed by 12, 36, and 48 weeks of follow-up. The statistical significance is defined as *P* < 0.05, and the 95% confidence interval will be reported.

Many MRI studies have reported statistical significance with 12 to 21 patients per group [23, 58–60]. To have a powerful and repeatable statistical effect, we require 25 patients per group in this trial. Considering a 20% dropout rate and the possible excessive head motion during scanning, it will include 30 KOA participants in each group. In summary, we plan to enroll 60 participants, and each group will undergo MRI scans to investigate different central mechanisms between Tuina and healthcare education treatments.

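### The stated inputs require 18 or 19 per group, not 25, and 30 per group leaves 24 after the stated 20% dropout; under those inputs the error is conservative

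*Protocol article*

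**What the plan says.** The calculation is in the Sample size section of the protocol article.

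- Test: a two-sided comparison of two means ("The calculation method of bilateral equality of two samples is adopted").
- Error rates: "0.05 as the type I error" and "0.90 as the power".
- Expected VAS changes: "12 weeks of Tuina as μA = 3" and "healthcare education intervention as μB = 0.7".
- Spread: the standard deviation "of the two groups is equal, i.e., *σ*=2.1".
- Result: "the final result is that we need at least 25 samples in each group".

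The next paragraph of the section mentions the group sizes of earlier MRI studies, repeats 25 per group as the requirement, and moves to enrolment: "Considering a 20% dropout rate and the possible excessive head motion during scanning, it will include 30 KOA participants in each group". The total is 60. Allocation is 1:1 (Participant recruitment), and the primary comparison is at one timepoint, week 12 (Primary outcome measurement).

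**The concern.** The section prints a full set of inputs and a result, so the result can be checked, and it does not follow from the inputs. The gap is 6 or 7 patients per group, too large to be rounding. A reader cannot tell which printed number is wrong, and so cannot say what effect the trial was really sized to detect.

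The step from 25 to 30 has a fault of its own. It multiplies by 1.2 where a 20% loss calls for division by 0.80, so the enrolled number does not deliver the minimum stated just before it.

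At stake is the justification of the sample size for the primary outcome: whether the stated 90% power describes this design, and whether the evaluable number matches the requirement.

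**Working it through.** **Inputs** (Sample size section): difference = 3 − 0.7 = 2.3; SD = 2.1; two-sided alpha 0.05 (z = 1.960); power 0.90 (z = 1.2816); equal groups.

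**Step 1. Attempt to reproduce 25.**

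n per group = 2 × (1.960 + 1.2816)² × 2.1² / 2.3² = 17.52, so 18.

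With the exact (noncentral t) calculation, 18 per group gives 89.1% and 19 gives 90.7%, so 19 are needed. The stated 25 is not reproduced.

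**Step 2. Power under the stated inputs.**

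| Per group | Normal approximation | Exact t |
|---|---|---|
| 18 | 90.8% | 89.1% |
| 19 | 92.2% | 90.7% |
| 24 | 96.7% | 96.0% |
| 25 | 97.2% | 96.7% |

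**Step 3. What would give 25?** The following do, and none is stated in the article:

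- SD of about 2.5: 2 × (1.960 + 1.2816)² × 2.5² / 2.3² = 24.8, so 25 (normal approximation).
- Difference of about 2.0 with SD 2.1: 24 (normal) or 25 (exact t).
- Two-sided alpha 0.01: 25 (normal).
- Alpha divided by 3: 25 (exact t). Alpha divided by 5: 25 (normal).
- Dropout already included in the 25: 20/0.80 = 25, although the formula gives 18 or 19, not 20, and the 20% would then have been applied twice.

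A one-sided test at 0.05 goes the other way, to 15 or 16. Inflating 18 or 19 for a rank test at its worst-case efficiency of 0.864 gives 20.8 or 22.0, still short of 25.

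**Step 4. Dropout.**

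- Enrolled figure: 25 × 1.2 = 30.
- Evaluable after 20% loss: 30 × 0.80 = 24.
- Needed to keep 25 evaluable: 25/0.80 = 31.25, so 32 per group (64 in total).
- Needed for the minimum that the inputs imply: 18/0.80 = 22.5, so 23; 19/0.80 = 23.75, so 24.

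**The case against.** The strongest reply is that nothing is lost. Under the only inputs given, 30 per group is more than enough: power stays above 90% down to 19 evaluable per group, so 11 of 30 (37%) could be lost before the stated power is missed. The dropout slip costs one patient per group, and it matters only if 25 is truly the requirement, which the stated inputs deny. All of this stands, and it limits the point to a reporting error.

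Two other defences do not succeed. One is that 25 was chosen for the imaging outcomes. The section gives 25 as the outcome of the VAS calculation before it turns to MRI studies, and only then repeats it. The other is that a journal article condenses the protocol. Nothing is missing here; the inputs and the result are both printed, and they disagree.

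A reader might go further and infer that the trial is underpowered, on the view that the SD really used was about 2.5. With that SD, exact t power is 89.0% with 25 per group and 87.7% with 24. The document does not support this inference. It states 2.1; 2.5 is obtained only by solving backwards from 25, and Step 3 shows several other routes to the same number. Even under that assumption the exact t figure is already below 90% with 25 per group, so the dropout slip would not be what causes the shortfall.

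Nor do scans lost to head motion reduce the power for VAS. They remove imaging data, not pain scores, and the section makes no power claim for the imaging outcomes.

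**Conclusion.** The point holds as an error in the stated figures. The printed inputs require 18 per group (normal approximation) or 19 (exact t), against a stated 25, and 30 per group less 20% leaves 24, below the minimum that the section states twice. The first mismatch is the material one; the second is one patient per group.

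If the stated inputs are right, the error is conservative: about 96% power with 24 per group and about 97% with 25, where the text claims 90%. The primary VAS comparison at week 12 is then not at risk. This rests on the printed difference of 2.3, SD of 2.1 and unadjusted two-sided alpha of 0.05, and on a two-sample comparison of changes at that one timepoint. If one of these is the misprinted figure, the power cannot be known until the true value is given.

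**What to change.** Correct the text of the Sample size section and leave enrolment at 60. Which correction applies depends on what the sponsor's calculation used.

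1. **If the printed inputs are right:** change the required minimum to 18 per group (normal approximation) or 19 (exact t), name the method, and state that 30 randomised per group, 24 evaluable after 20% dropout, give about 96% power.
2. **If 25 came from a different SD, difference or alpha:** print those inputs and restate the power at the 24 evaluable per group that the dropout assumption delivers.

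In either case, keep the required minimum apart from the number expected to remain after dropout, and compute the dropout allowance as n/(1 − 0.20). Simply writing 24 in place of 25 as the minimum would not do, because 24 does not follow from the printed inputs either.

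The cost is a text correction, with no change to recruitment, conduct or analysis.

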### Randomisation

A total of 60 eligible participants will be assigned to the Tuina or Education groups at 1:1 ratio using stratified randomisation with gender and age as factors in this research. Stratified randomisation is achieved by performing a separate randomisation procedure within each of two subsets of participants (gender and age). First, participants will be grouped by gender. Then, male and female participants will be grouped by age. After grouping, there will be four subgroups: (1) men aged < 50, (2) men aged ≥ 50, (3) women aged < 50, and (4) women aged ≥ 50. In these four subgroups, the subjects will be randomly divided into the Tuina group and Education group. Finally, all Tuina groups and Education groups are merged to form a new Tuina group and Education group. This step ensures good balance amongst participant characteristics in each group and close balance amongst the numbers of participants receiving each intervention within each stratum. The created random number lists will be generated by a random number generator (IBM SPSS Statistics version 21.0 software; IBM Corp., Armonk, NY, USA) and will be sent to the therapist with sequentially numbered, opaque, and sealed envelopes by an independent assistant. The therapist will open random-allocation envelopes and allocate the participants accordingly to the Tuina or Education group.

### Blinding

Participants and therapists will not be blinded to treatment allocation, because of the features of the Tuina treatment and the education intervention. For participants, their subjective consciousness will affect the outcomes, which is unavoidable. Nevertheless, the evaluators, data managers, and statisticians will be blinded to the group allocation in the outcome evaluation procedure and data analysis throughout the entire procedure to reduce the risk of bias. The data will not be accessible to the evaluators until the collection is finished.

